**SENS-BTK Prospective Clinical Study Protocol**

1. **Study Title**

Efficacy of **S**elf-**E**xpanding **N**itinol **S**tent versus Balloon Angioplasty Alone for the **B**elow **T**he **K**nee Arteries following Successful Balloon Angioplasty Trial (**SENS-BTK** trial): Korean Prospective Randomized Multicenter Clinical Trial

1. **Backgrounds**

While endovacular interventions (EVT) and clinical research for peripheral vascular diseases (PVD) of the iliac and femoropopliteal arteries are common, there are relatively limited number of EVT and clinical research for the below-the-knee (BTK) arteries. Nowadays, the interests for the BTK intervention is rapidly increasing due to increased prevalence of diabetes mellitus (DM) world widely and active screening program in high volume centers. Recently, favorable outcomes following EVT have been reported in critical limb ischemia patients, especially those with diabetes as comorbidity or who are not eligible for bypass surgery.

Percutaneous transluminal balloon angioplasty (PTA) has been increasingly performed over the past decades since small-sized profile catheters, hydrophilic guide wires, balloons, stents and other innovative devices were introduced. Also in the infrapopliteal arteries, stenting is applied in case that it has been failed to restore anterograde flow even after the balloon angioplasty with a conventional endovascular intervention technique. In the past, stents for the below-the-knee vessels only was not introduced in South Korea; however, self-expanding nitinol stent for such the small infrapopliteal vessels (Xpert Stent, AbbottVascular, San Francisco, Calif., USA) has become commercially available in recent days.

According to a report of the outcomes of conventional balloon angioplasty for the infrapopliteal arteries in patients with critical limb ischemia, the procedural success rate was estimated at 93%; restenosis, revascularization and lower limb amputation rates at 12 months 39%; vascular patency rate at 12 months 53%; and, as secondary endpoints, restenosis and revascularization rates at 12 months 63% and 61%, respectively. It was also reported that limb salvage rate was 84% at 12 months (J Vasc Interv Radiol 2007; 18:703–708). Although the conventional balloon angioplasty exhibits approximately 90% of good limb salvage rate as described above, it shows actually unsatisfactory primary vascular patency rates and more unfavorable outcomes in long and complex lesions.

In addition, it is reported that the failure rates of conventional balloon angioplasty for the infrapopliteal arteries range from 10% to 40% depending on lesion type and surgeon’s experience. Besides, in case of severe calcification, residual stenosis ≥50%, dissection leading to blood flow disturbances, or occlusive thrombus formation not responsive to thrombolysis, thrombus aspiration or balloon angioplasty, stenting is usually attempted following balloon angioplasty. Because of concern about early thrombus formation resulting from stent placement in the small-diameter infrapopliteal arteries and possible late lumen loss caused by intimal hyperplasia, routine stenting in the infrapopliteal arteries are not being widely spread.

The self-expanding nitinol stent for the below-the-knee arteries were developed for the purpose of maintaining stable blood flow, preventing lumen loss and ultimately improving vascular patency rate. When the self-expanding stent was implanted in 16 patients with critical limb ischemia who were not respond to conventional balloon angioplasty, the vascular patency rate at 6 months was obtained from 14 patients of them, and good patency was observed in 12 lesions.

In a study of below-the-knee artery balloon angioplasty followed by routine (self-expanding) stenting in 47 patients with critical limb ischemia as it was expected that it would contribute significantly to good clinical outcomes, it was found that the vascular patency and limb salvage rates were 76.3% and 95.9% at 12 months, and 54% and 90.8% at 24 months, respectively

As mentioned above, with the recent advances of medical technologies and the introduction of self-expending stents only for the infrapopliteal arteries, vascular interventions in critical limb ischemia are radically developing. However, the gold standard therapy has not been established yet like that for coronary artery interventions. Moreover, there is currently a lack of comparative studies of balloon angioplasty alone *versus* balloon angioplasty with routine stenting – the former is that it is left as it is in the case of good responses to balloon angioplasty and the latter is that stenting is routinely conducted after balloon PTA, similarly to coronary artery intervention.

In the context above, the present investigators attempted to identify the effects of conventional balloon angioplasty with self-expanding nitinol stent in the occlusive lesions of the infrapopliteal arteries in patients with critical limb ischemia, in the manner of collecting case data and analyzing comparatively patient groups treated with balloon angioplasty alone versus balloon angioplasty with routine stenting in a prospective multicenter randomized clinical trial.

1. **Study Objectives**

The objectives of this study are to compare directly conventional balloon angioplasty alone *versus.* balloon angioplasty with routine stenting – that is, to determine whether angioplasty with self-expanding stent is superior to conventional balloon angioplasty - in the infrapopliteal arterial occlusive lesions of critical limb ischemia patients by collecting and analyzing the cases of each patient group in a prospective multicenter randomized clinical trial, and to clarify main factors affecting mid- and long-term clinical effects of angioplasty with self-expanding stent in the infrapopliteal arteries.

Hypothesis: Balloon PTA followed by routine stenting with self-expanding nitinol stent in critical limb ischemia patients with infrapopliteal arterial occlusive lesions is superior to conventional PTA followed by provisional stenting, in the aspect of vascular restenosis rate.

1. **Study Sites and Period:**

Korean, national, multicenter prospective randomized clinical trial

Study Period: From Sept 2011 to July 2014

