   12. Significant leucopenia, neutropenia, thrombocytopenia, anemia, or known bleeding diathesis
   13. Life expectancy <1 year due to comorbidity
2. Angiographic criteria
   1. Reference segment diameter is not suitable for available stent design
   2. Previously implanted stent(s) or PTA at the same lesion site
   3. Inflow-limiting arterial lesions left untreated
3. **Sample Size Estimation**

On the assumption that the restenosis rate at 12 months after the conventional balloon angioplasty for the infrapopliteal arterial occlusive lesions in patients with critical limb ischemia is estimated approximately at 55%, whether the restenosis rate at 12 months after balloon angioplasty with routine stenting with self-expanding stent is higher than (superior to) that of the conventional balloon angioplasty alone is tested with 80% of power (20% of difference). When computed in ‘Power and Precision V4’ software program to do so, the sample size required is 89 for each group, and in consideration for drop-outs including 30% of follow up loss, the sample size (number of subjects) computed was 116 per group and a total of 232. For the statistical computation method, see the Appendix.

1. **Study Design and Methodology**

- Study design: A prospective multicenter randomized controlled trial

- Study methodology: Critical limb ischemia patients with infrapopliteal arterial occlusive or stenotic lesions at the participating centers between November 2011 and January 2015 are randomly assigned to a group of patients who will undergo provisional stenting following conventional balloon angioplasty and the other group of patients who will undergo routine stenting following conventional balloon angioplasty. Then, for each group, preoperative clinical and lesion characteristics will be investigated at baseline, the intervention procedures, immediate postoperative results, the length of hospital stay, clinical outcomes/course after discharge, and revascularization rates will be evaluated, and the restenosis rate will be angiographically examined at 12 months, followed by analyzing comparatively any factors affecting the rate.

[figure not shown]

1. **Monitoring/Laboratory and Clinical Parameters**

- Symptom diagnosis: according to Rutherford & Fontaine classification

- Preoperative clinical characteristics at baseline

- Lesion characteristics based upon the findings of imaging

- Intervention procedure related parameters

- Postoperative outcomes/course

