1. Imaging parameter (CT, color Doppler): >50% restenosis at 12 months
2. Hemodynamic parameter: Ankle-brachial index, Calf-brachial index, Thigh-brachial index
3. Clinical outcomes/course:
   1. Symptom recurrence or aggravation
   2. Target vessel revascularization
   3. Major cardiovascular adverse events : death, MI, stroke
   4. Lower limb amputation status
4. **Efficacy Evaluation Criteria/Method and Analysis Techniques**

1. Primary endpoint: Binary restenosis at 12 months

Binary restenosis : >50% re-obstruction of the target lesion as assessed by quantitative

angiography

2. Secondary endpoints

1. Target vessel revascularization rate
2. Limb salvage rate: free from amputation
3. Major cardiovascular adverse events : death, MI, stroke
4. Angiographic variables (Binary restenosis, FU MLD, LL, % restenosis)

3. Statistical analysis

Categorical variables will be expressed in percentage, and inter-subgroup comparisons will be analyzed with either Chi-square or Fisher’s exact test. Continuous variables will be expressed in mean ± standard deviation, and inter-subgroup comparisons will be analyzed with Student’s *t* test. In addition, clinical course and outcomes including patient’s symptoms, restenosis assessed based on the findings on ABI and invasive angiograms, target vessel revascularization, major cardiovascular adverse events (death, MI and stroke) and lower limb amputation status will be analyzed with Kaplan-Meier survival estimates, and inter-subgroup comparisons will be analyzed with log-rank test. *p* value <0.05 will be considered statistically significant.

1. **Data Management**

In order to ensure confidentiality of research data, all the personal information of patient data collected will be encoded, recorded and kept so that they cannot be disclosed easily. Additionally, all electronic (computed) data will be saved in a computer to which access will be restricted, and all documentary data will be stored in a locking system.

1. **Study Implementation Plan**

|  | 2011  11 |  |  | 2012  9 |  |  | 2013  8 |  |  |  | 2014  11 | 2015  1 |
| --- | --- | --- | --- | --- | --- | --- | --- | --- | --- | --- | --- | --- |
| Patient enrollment |  |  |  |  |  |  |  |  |  |  |  |  |
| Data collection and analysis |  |  |  |  |  |  |  |  |  |  |  |  |
| Paper Writing |  |  |  |  |  |  |  |  |  |  |  |  |

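### The study period, randomisation window and timetable cannot all hold with a 12-month angiographic primary endpoint

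*Combined protocol and SAP*

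**What the plan says.** Three places in the combined protocol and SAP carry operating dates.

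- **Study Sites and Period:** "Study Period: From Sept 2011 to July 2014".
- **Study Design and Methodology:** patients are taken in "between November 2011 and January 2015 are randomly assigned" to the two arms. The same paragraph says "the restenosis rate will be angiographically examined at 12 months".
- **Study Implementation Plan:** the legible column heads are November 2011, September 2012, August 2013, November 2014 and January 2015. The rows are enrolment, data collection with analysis, and paper writing. The marking that shows when each activity runs did not survive in the text available for review, which is not a fault of the plan.

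The Efficacy Evaluation section sets "Primary endpoint: Binary restenosis at 12 months", assessed by quantitative angiography. The Sample Size Estimation section gives a planned enrolment that "computed was 116 per group and a total of 232", built on the statement that "the sample size required is 89 for each group".

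The start dates differ too: September 2011 in one section, November 2011 in the other two. No accrual rate, angiogram window or data cut-off date is stated, and neither is a rule for when the primary analysis is triggered.

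**The concern.** Read as written, the study closes six months before randomisation ends, and the last patients' primary endpoint falls due after every end date in the document. There are then two possibilities. If the dates act as cut-offs, late enrollees contribute no 12-month angiogram, in addition to the 30% follow-up loss already allowed for. If the analysis waits for those patients, the stated period and the timetable are wrong. Either way something needs correcting, and the plan does not say which. The primary comparison depends on the answer, because the trial needs 89 evaluable patients per group at 12 months.

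**Working it through.** **1. The dates side by side**

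- Last randomisation as written: January 2015. Adding 12 months gives January 2016 for the last primary-endpoint angiogram.
- Stated study end: July 2014. The gap to January 2016 is 18 months, and randomisation itself runs 6 months past this date.
- Last timetable column: January 2015. The gap to January 2016 is 12 months. Wherever the lost bars lay, no bar in a table ending January 2015 can include a January 2016 angiogram.

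The contradiction needs no assumption about accrual.

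**2. The plan's own figure**

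The plan states no share of patients who would miss the 12-month visit, so there is none to reproduce. Its evaluable target does reproduce. With 55% vs 75%, two-sided alpha 0.05, 80% power and pooled variance without continuity correction:

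n = [1.960·√(2·0.65·0.35) + 0.842·√(0.55·0.45 + 0.75·0.25)]² / 0.20² = 88.1, rounded up to 89 per group (power 80.4%).

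The date problem does not alter that number. It bears only on whether 89 per group would have an endpoint.

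**3. Illustrative share affected**

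Assumptions, neither of them in the documents: accrual is uniform over the randomisation window as written, and the end date is enforced as a data cut-off.

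- Window November 2011 to January 2015 inclusive: 2 + 36 + 1 = 39 months.
- Cut-off July 2014: patients randomised from August 2013 on cannot reach 12 months. 5 + 12 + 1 = 18 months; 18/39 = 46%; 232 × 18/39 ≈ 107 patients. Counting month ends differently gives 45% to 49%.
- Cut-off January 2015: 12/39 = 31%; 232 × 12/39 ≈ 71 patients (31% to 32%).

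The two figures belong to different end dates and do not form one range.

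**4. Other readings of the same dates (uniform accrual)**

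- Enrolment also stops in July 2014: the window is 33 months and 12/33 = 36% miss 12 months by July 2014.
- Enrolment stops about August 2013 (an assumption suggested by a column head): the window is 22 months; 1/22 ≈ 5% miss July 2014 and none miss January 2015.
- Back-loaded accrual would push the July 2014 figure above 46%; front-loaded accrual would lower it.

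**5. What the illustration would mean for power**

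Using the Appendix rates and the step 3 assumptions:

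| Cut-off | Per group reaching 12 months | Power, no other loss | Power, 30% also lost |
|---|---|---|---|
| January 2015 | 116 × 27/39 ≈ 80 | 76% | 60% (n = 56) |
| July 2014 | 116 × 21/39 ≈ 62 | 65% | 50% (n ≈ 43) |

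**The case against.** The strongest reply is that this is a wording slip with no effect on the analysis. November 2011 and January 2015 are exactly the first and last column heads of a timetable that covers the whole project, including writing the paper. The Study Design sentence may simply have attached the project span to randomisation. The intermediate heads could mark phases: enrolment to about August 2013, data collection to November 2014, writing to January 2015. The last angiogram would then fall in August 2014, inside the timetable. In addition, nothing in the document sets a data cut-off or permits analysis before 12 months, and the endpoint is fixed at 12 months.

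Much of this stands. The phase reading is an inference, but it cannot be excluded, and under it few or no patients are affected. The 46% figure is also awkward on its own terms: it requires July 2014 to bind as a cut-off while 6/39 = 15% of patients are randomised after it.

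The reply does not remove the contradiction. If January 2015 is the project end, the randomisation dates in Study Design and Methodology are wrong and need correcting. The July 2014 study end would still conflict with a project running to January 2015, and would still fall before an August 2014 angiogram.

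**Conclusion.** The point holds as a contradiction in operating dates: the three statements cannot all be true with a 12-month angiographic primary endpoint. This follows from the dates alone.

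A reader might infer that up to 31–46% of patients will lose their primary endpoint. The documents do not support that. The percentages depend on uniform accrual, on the randomisation window being literally as written, and on an administrative date overriding the 12-month endpoint. None of these is established, and neither figure is an upper bound. Nor do the documents show that follow-up would be cut short. The share affected is unknown; it could be none, if enrolment in fact ended early enough. The 46% (July 2014) and 31% (January 2015) figures only indicate what would be at risk if the written dates were enforced. The sample size of 89 per group is not in question here.

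**What to change.** Reconcile Study Sites and Period, Study Design and Methodology, and the Study Implementation Plan into one set of dates: first randomisation, last randomisation, last 12-month angiogram and study end. Study end should be at least 12 months after last randomisation, plus any angiogram window allowed (none is defined at present). There are two routes:

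- **Correct the end of randomisation.** To keep July 2014 as study end, last randomisation would be about July 2013, which leaves 21 of the 39 months for enrolment. To keep January 2015, it would be January 2014 at the latest, and earlier if analysis and writing are to finish by then.
- **Keep randomisation to January 2015.** The study period and timetable then need to run to at least early 2016.

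In either case, state that the primary analysis is done only after the last randomised patient's 12-month angiogram is due.

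The cost is a protocol amendment to the dates and possibly a later study end. Treatment is unchanged and no procedures are added.

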**Participating centers:**

|  | Participating centers (sites) | Principal investigators | Co-investigators |
| --- | --- | --- | --- |
| **1** | Korea University Guro Hospital | [name] | [name] |
| **2** | Kwandong University MyoungJi Hospital | [name] |  |
| **3** | KonKuk University Chungju Hospital | [name] |  |
| **4** | Soonchunhyang University Cheonan Hospital | [name] | [name] |
| **5** | Yonsei University Shinchon Severance Hospital | [name] | [name] |
| **6** | Yonsei University Gangnam Severance Hospital | [name] |  |
| **7** | KyungHee University Medical Center | [name] |  |
| **8** | Gachon University Gil Hospital | [name] | [name] |
| **9** | Sam Medical Center, AnYang | [name] | [name] |
| **10** | SamSung Medical Center | [name] |  |
| **11** | Eulji University Hospital | [name] |  |
| **12** | Sejong General Hospital | [name] | [name] |
| **13** | Incheon Sarang Hospital | [name] |  |
| **14** | Pusan National University Hospital | [name] |  |

1. **Inclusion/Exclusion Criteria**

*a. Inclusion criteria*: All of the criteria listed below shall be met.

1. Clinical criteria
   1. Age 20 years of older
   2. Symptomatic critical limb ischemia (Rutherford 4 - 6)
   3. Patients with signed informed consent
2. Anatomical criteria
   1. Target lesion length < 8 cm by angiographic estimation
   2. Stenosis of >50% or occlusive atherosclerotic lesion of the ipsilateral infrapopliteal artery
   3. Reference vessel diameter should be 2.0–4.5 mm.

*b. Exclusion criteria:*

1. Clinical criteria
   1. Patient has a known allergy to heparin, aspirin, or other anticoagulant/antiplatelet therapies or a bleeding diatheses or is unable, or unwilling, to tolerate such therapies
   2. Patient takes warfarin
   3. Patient has a history of previous life-threatening contrast media reaction
   4. Patient is currently enrolled in another investigational device or drug trial
   5. Patient is currently breast-feeding, is pregnant, or intends to become pregnant
   6. Patient is mentally ill or retarded
   7. Acute critical limb ischemia
   8. Major bleeding history within prior 2 months
   9. Age > 80 years
   10. Severe hepatic dysfunction (> 3 times normal reference values)
   11. Serum creatinine level ≥ 3.0 mg/dl or dependence on dialysis
   12. Significant leucopenia, neutropenia, thrombocytopenia, anemia, or known bleeding diathesis
   13. Life expectancy <1 year due to comorbidity
2. Angiographic criteria
   1. Reference segment diameter is not suitable for available stent design
   2. Previously implanted stent(s) or PTA at the same lesion site
   3. Inflow-limiting arterial lesions left untreated
3. **Sample Size Estimation**

On the assumption that the restenosis rate at 12 months after the conventional balloon angioplasty for the infrapopliteal arterial occlusive lesions in patients with critical limb ischemia is estimated approximately at 55%, whether the restenosis rate at 12 months after balloon angioplasty with routine stenting with self-expanding stent is higher than (superior to) that of the conventional balloon angioplasty alone is tested with 80% of power (20% of difference). When computed in ‘Power and Precision V4’ software program to do so, the sample size required is 89 for each group, and in consideration for drop-outs including 30% of follow up loss, the sample size (number of subjects) computed was 116 per group and a total of 232. For the statistical computation method, see the Appendix.

1. **Study Design and Methodology**

- Study design: A prospective multicenter randomized controlled trial

- Study methodology: Critical limb ischemia patients with infrapopliteal arterial occlusive or stenotic lesions at the participating centers between November 2011 and January 2015 are randomly assigned to a group of patients who will undergo provisional stenting following conventional balloon angioplasty and the other group of patients who will undergo routine stenting following conventional balloon angioplasty. Then, for each group, preoperative clinical and lesion characteristics will be investigated at baseline, the intervention procedures, immediate postoperative results, the length of hospital stay, clinical outcomes/course after discharge, and revascularization rates will be evaluated, and the restenosis rate will be angiographically examined at 12 months, followed by analyzing comparatively any factors affecting the rate.

[figure not shown]

1. **Monitoring/Laboratory and Clinical Parameters**

- Symptom diagnosis: according to Rutherford & Fontaine classification

- Preoperative clinical characteristics at baseline

- Lesion characteristics based upon the findings of imaging

- Intervention procedure related parameters

- Postoperative outcomes/course

1. Imaging parameter (CT, color Doppler): >50% restenosis at 12 months
2. Hemodynamic parameter: Ankle-brachial index, Calf-brachial index, Thigh-brachial index
3. Clinical outcomes/course:
   1. Symptom recurrence or aggravation
   2. Target vessel revascularization
   3. Major cardiovascular adverse events : death, MI, stroke
   4. Lower limb amputation status
4. **Efficacy Evaluation Criteria/Method and Analysis Techniques**

1. Primary endpoint: Binary restenosis at 12 months

Binary restenosis : >50% re-obstruction of the target lesion as assessed by quantitative

angiography

2. Secondary endpoints

1. Target vessel revascularization rate
2. Limb salvage rate: free from amputation
3. Major cardiovascular adverse events : death, MI, stroke
4. Angiographic variables (Binary restenosis, FU MLD, LL, % restenosis)

3. Statistical analysis

Categorical variables will be expressed in percentage, and inter-subgroup comparisons will be analyzed with either Chi-square or Fisher’s exact test. Continuous variables will be expressed in mean ± standard deviation, and inter-subgroup comparisons will be analyzed with Student’s *t* test. In addition, clinical course and outcomes including patient’s symptoms, restenosis assessed based on the findings on ABI and invasive angiograms, target vessel revascularization, major cardiovascular adverse events (death, MI and stroke) and lower limb amputation status will be analyzed with Kaplan-Meier survival estimates, and inter-subgroup comparisons will be analyzed with log-rank test. *p* value <0.05 will be considered statistically significant.

1. **Data Management**

In order to ensure confidentiality of research data, all the personal information of patient data collected will be encoded, recorded and kept so that they cannot be disclosed easily. Additionally, all electronic (computed) data will be saved in a computer to which access will be restricted, and all documentary data will be stored in a locking system.

1. **Study Implementation Plan**

|  | 2011  11 |  |  | 2012  9 |  |  | 2013  8 |  |  |  | 2014  11 | 2015  1 |
| --- | --- | --- | --- | --- | --- | --- | --- | --- | --- | --- | --- | --- |
| Patient enrollment |  |  |  |  |  |  |  |  |  |  |  |  |
| Data collection and analysis |  |  |  |  |  |  |  |  |  |  |  |  |
| Paper Writing |  |  |  |  |  |  |  |  |  |  |  |  |

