**Appendix**

**Sample size**

**Executive summary**

With a sample of 89 subjects per group the study will have power of 80%. This means that there is an 80% likelihood that the study will yield a statistically significant effect, and allow us to conclude that the percentage of subjects in 'Response A' differs for Group A versus Group B.

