**Absolute value of the proportions**

Another factor that determines the required sample size is the absolute value of the proportions. The sample size required to detect a 20 percentage points difference will be larger if the proportions fall near 50%, and will be smaller if the proportions fall near 0% or near 100%.The sample size of 89 is based specifically on the comparison of 55% vs. 75%.

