**Alpha**

Another factor that has an impact on the required sample size is alpha, the criterion used for statistical significance. We used an alpha of 0.05, which is often the default value, in computing the required sample size of 89 per group.

It is sometimes appropriate to select a more conservative criterion. For example, with alpha set at 0.01 the required sample size would be 132 per group. Conversely, it is sometimes appropriate to select a less conservative criterion. For example, with alpha set at 0.10 the required sample size would be 70 per group.

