**Tails**

The final factor we need to consider is whether the significance test is one-tailed or two-tailed. We assumed that the study will use a two-tailed test, which is usually appropriate, and computed the required sample size as 89 per group.

If it were appropriate to use a one-tailed test (with alpha at 0.05) the required sample size would be 70 per group.

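### The sample-size rates (55% v 75%) contradict the hypothesis of lower restenosis with stenting; either the 55% control rate or the stated 80% power is wrong

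*Combined protocol and SAP*

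**What the plan says.** - **Hypothesis (Study Objectives).** Routine stenting "is superior to conventional PTA followed by provisional stenting, in the aspect of vascular restenosis rate". The primary endpoint (Efficacy Evaluation Criteria/Method and Analysis Techniques) is binary restenosis at 12 months, so superiority means a lower percentage.
- **Sample Size Estimation.** Restenosis after conventional balloon angioplasty is taken as about 55%. Whether the rate with routine stenting "is higher than (superior to) that of the conventional balloon angioplasty alone is tested with 80% of power (20% of difference") is the question to be tested. The result is 89 per group.
- **Appendix, Group A and Group B.** Response A is 55% in Group A and 75% in Group B. Under Absolute value of the proportions: "The sample size of 89 is based specifically on the comparison of 55% vs. 75" (per cent). The Appendix does not say whether Response A is restenosis or patency, or which treatment is Group A and which is Group B.
- **Appendix, other settings.** "We used an alpha of 0.05, which is often the default value"; "We assumed that the study will use a two-tailed test, which is usually appropriate"; "With a sample of 89 subjects per group the study will have power of 80" (per cent).
- **Backgrounds.** For balloon angioplasty: "vascular patency rate at 12 months 53" (per cent), with 63% restenosis quoted from the same report. For routine self-expanding stenting: "the vascular patency and limb salvage rates were 76.3% and 95.9% at 12 months".

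**The concern.** The control rate and the direction of benefit on the primary endpoint are the basis of a sample size. Here, the main text calls 55% a restenosis rate and describes the stent rate as the higher one, and the Appendix supplies a matching 75%. The word and the input agree with each other, and both disagree with the hypothesis. Changing the one word would not be enough, because 55% restenosis with a lower stent rate is a different pair of proportions from the pair behind the 89. As written, a reader cannot tell which effect on restenosis the trial has 80% power to detect.

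**Working it through.** **Inputs.** Two-sided alpha 0.05 (z = 1.960) from Alpha and Tails; power 80% (z = 0.842) from Executive summary; equal groups; difference of 20 percentage points from Difference between groups.

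**Formula** (pooled variance, no continuity correction), with p̄ the mean of the two rates:

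n per group = [1.960·√(2p̄(1−p̄)) + 0.842·√(p₁(1−p₁) + p₂(1−p₂))]² / (p₁−p₂)²

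**Step 1. The plan's own figure, 55% v 75%.** p̄ = 0.65.
- √(2 × 0.65 × 0.35) = √0.455 = 0.6745; × 1.960 = 1.322
- √(0.2475 + 0.1875) = √0.435 = 0.6595; × 0.842 = 0.555
- n = (1.877)² / 0.04 = 88.1, so **89**. Power at 89 is 80.4%.

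The same formula returns the Appendix's alternatives for this pair: 132 at alpha 0.01, 70 at alpha 0.10 and 70 one-tailed. The method is therefore identified.

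**Step 2. The mirror image, 45% v 25%.** Replacing each rate by its complement leaves every p(1−p) term and the difference unchanged, so n is again 88.1, or **89**. If 55% and 75% are patency, and restenosis is taken as the complement of patency, this is the restenosis comparison that was powered.

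**Step 3. A 20-point benefit from 55% restenosis, 55% v 35%.** p̄ = 0.45.
- √(2 × 0.45 × 0.55) = √0.495 = 0.7036; × 1.960 = 1.379
- √(0.2475 + 0.2275) = √0.475 = 0.6892; × 0.842 = 0.580
- n = (1.959)² / 0.04 = 95.9, so **96**, which is 7 more per group (7/89 = 7.9%).
- Power at 89: z = (0.20·√89 − 1.379) / 0.6892 = (1.887 − 1.379) / 0.6892 = 0.737, giving **76.9%**.

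The number rises because 55% and 35% lie closer to 50% than 55% and 75% do; the Appendix states this principle itself. The choice of formula does not rescue 89: for 55% v 35%, the unpooled formula gives 94, arcsine 96, continuity-corrected 106, and one-sided 76.

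**Step 4. The readings side by side.**

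| Reading of 55 and 75 | Restenosis, balloon v stent | n for 80% power | What must change |
| --- | --- | --- | --- |
| Restenosis, taken literally | 55% v 75% | 89 | Contradicts the hypothesis |
| Patency | 45% v 25% | 89 | The 55% control restenosis rate |
| 55% restenosis, 20-point benefit | 55% v 35% | 96 | The 80% power at 89 |

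No row leaves every statement in the plan intact.

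**The case against.** The strongest reply is that this is a labelling slip with no operational effect. The 89 reproduces exactly. The test is two-tailed and asks only whether the proportions differ, so neither the number nor the analysis depends on the word *higher*. The gloss in brackets and the hypothesis both show that benefit was intended. If the rates are patency, the sample size is simply right. All of this stands, and it limits the point to the inputs and their label. It does not remove the point, because on the patency reading the stated 55% control restenosis is wrong by 10 points.

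Two stronger readings are tempting, and the documents support neither.

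- **That the trial was designed to show harm from stenting.** A reader might infer this from 75% in Group B. But the Appendix never says that Response A is restenosis or that Group B is the stent arm, and the hypothesis states the opposite direction.
- **That the trial is too small.** The shortfall of 7 per group exists only on the 55% v 35% reading. The planned enrolment of 116 per group would still leave 96 evaluable after losing 20 of 116 (17%). The plan does allow for 30% loss, but how 89 was inflated to 116 is a separate matter and is not counted here.

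The patency explanation should not be pressed too far either. The background values of 53% and 76.3% are close to 55% and 75%, which makes it plausible. But the plan calls 55% approximate, and the balloon report is quoted with 53% patency and 63% restenosis, which sum to 116%. Patency and restenosis are therefore not complements in that source, and the background cannot settle what was meant.

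**Conclusion.** Wrong as written. The sample-size inputs contradict the primary hypothesis, and the documents do not show which rates were intended. The arithmetic for 55% v 75% is correct, and direction alone does not alter the number under a two-sided test.

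The size depends on the reading. If the rates are patency, the sample size is unaffected and the control restenosis assumption moves from 55% to 45%. If 55% restenosis is meant, 80% power needs 96 evaluable per group, and 89 gives about 77%, roughly 3 points below the stated 80%. Both results assume two-sided alpha 0.05, the pooled formula that reproduces the plan's figures, and an absolute difference of 20 points. The first also assumes that restenosis is the complement of patency. The inconsistency is certain; a loss of power is conditional.

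**What to change.** 1. In Sample Size Estimation, replace the phrase saying the stent rate is higher than (superior to) the balloon rate with *lower than*.
2. In the Appendix, define Response A and say which treatment is Group A and which is Group B.
3. State the intended 12-month restenosis rates, balloon v stent, as one of:
   - *45% v 25%*, keeping 89 per group and correcting the 55% control restenosis rate in the main text; or
   - *55% v 35%*, restating power at 89 evaluable per group as about 77%, without enrolling more. The Appendix figures would then be rerun for this pair: 96 for 80% power, 144 at alpha 0.01, 76 at alpha 0.10 and 76 one-tailed.

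The sponsor must choose between them, because the documents do not. The cost is wording in the protocol and Appendix and, under the second option, a less favourable stated power. The allowance for 30% loss should be dealt with separately.
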